#### Safety assessment

All participants will report any adverse events that they experience while undergoing the intervention at every visit. Every adverse event will be described in the CRF. If the adverse event is severe and associated with the trial, the participant will be withdrawn from the trial, and the appropriate treatment will be given to him or her. For the safety assessment, a liver function test, blood cell count test and physical examination will be performed at Visits 1, 2 and 5. The safety-related variables will be analysed using the ITT method.

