### Subject withdrawal criteria

The subjects who meet the criteria listed in Subject withdrawal criteria section will be discontinued from treatment. The participants who are withdrawn after randomisation will be followed for outcomes.

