### Safety outcomes

All variables related to the safety assessment, such as vital signs, physical examinations, laboratory tests (complete blood cell count, liver function test, renal function test) and adverse events (AEs) will be documented on the case report form (CRF) at every visit.

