### Statistical analysis

#### Efficacy assessment

Statistical analyses will be performed for both the ITT (intention-to treat, all randomly assigned participants) and PP (per-protocol, participants completed the trial without any protocol deviations) data sets. The missing values will be imputed by the last observation carried forward (LOCF) method. The continuous variables will be displayed as the mean ± SD(standard deviation), and the categorical variables will be displayed as the n (%). The baseline characteristics will be compared by either a Student’s *t*-test for continuous variables or the χ^2^ test (Fisher’s exact test will be used when the expected value is < 5) for the categorical data. Alternatively, McNemar’s test will be used if the normality assumption is not satisfied for the continuous variables. For the primary outcome measures, the mean differences from the baseline values to the end of treatment will be compared using an independent T-test.

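### Safety is assigned to everyone randomised rather than everyone exposed, and the per-protocol set excludes for any deviation; both definitions should be replaced

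*Protocol article*

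**What the plan says.** **Safety set.** The Safety assessment section of the protocol article closes with: "The safety-related variables will be analysed using the ITT method". The Efficacy assessment section defines the two sets the article uses: "intention-to treat, all randomly assigned participants) and PP (per-protocol, participants completed the trial without any protocol deviations) data sets". No set is defined by intake of product.

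**Adverse event recording.** The Safety assessment section says: "All participants will report any adverse events that they experience while undergoing the intervention at every visit". It adds that a participant with a severe, trial-related event leaves the trial. The Subject withdrawal criteria section describes stopping treatment and then says: "The participants who are withdrawn after randomisation will be followed for outcomes". The Safety outcomes section says that adverse events and the other safety variables "will be documented on the case report form (CRF) at every visit". Table 1 schedules adverse event recording at Visits 3, 4 and 5.

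**Per-protocol set.** Membership requires both completion and the absence of any deviation. The list of withdrawal criteria, by contrast, speaks of violations that are significant.

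**The concern.** A safety analysis asks what happened to people who were exposed, according to what they were exposed to. An all-randomised set answers a slightly different question. Never-dosed participants add to the denominator but cannot have an event caused by the product, and a dispensing error places an event in the wrong arm. Both tend to blur a difference in harm, and safety is half of the trial's stated aim.

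The per-protocol rule has a different weakness. Read as written, it gives a trivial deviation the same consequence as use of a forbidden treatment. It also requires completion, so it removes people who stopped because of adverse events, and such stops may differ between arms. The result is a smaller set, selected after randomisation and partly for reasons unrelated to whether the treatment was taken as intended.

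**Working it through.** **The plan's own figure.** Inputs from the Sample size section: difference 10, SD 13.576, 80% power, 5% significance, 10% dropout.

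- n = 2(z_α/2 + z_β)²σ²/Δ² gives 28.932 per group with unrounded normal quantiles, as printed. The rounded values 1.96 and 0.84 give 28.899. Both round up to 29.
- 29 / 0.9 = 32.2, so 33 per group and 66 in total.

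The figure reproduces and is not in dispute. It supplies the 33 per arm used below.

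**Never-dosed participants.** Assumptions not in the article: a 20% event rate among the dosed, and u of 33 per arm never dosed and without events. Displayed rate = 0.20 × (33 − u)/33.

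| u | Displayed rate |
|---|---|
| 0 | 20.0% |
| 1 | 19.4% |
| 2 | 18.8% |
| 3 | 18.2% |

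**Wrong product.** One event in a participant given the other arm's product shifts about 1/33 = 3.0 percentage points to the wrong arm. The article gives no rate for such errors.

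**Who differs between the two sets.** Table 1 places randomisation at Visit 2 (day 0), the start of the treatment period. An all-randomised set and an exposed set therefore differ only by the never-dosed and the misallocated. Participants who start product and stop early are in both.

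**Adverse event passages side by side.**

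- Safety assessment: reporting is tied to the time on intervention, and a severe related event takes the participant out of the trial.
- Subject withdrawal criteria: the participant is taken off treatment but still followed.
- Safety outcomes and Table 1: recording at visits, with no on-product condition.

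These can be read together if time on intervention means the 8-week treatment period and follow-up for outcomes includes safety. They conflict if the first is read literally. The text does not settle which is meant.

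**Per-protocol size.** The 10% allowance is for dropout, with no separate allowance for deviations. With the plan's difference and SD, power = Φ(Δ/(σ√(2/n)) − 1.96):

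| n per arm in PP | Power |
|---|---|
| 29 | 80.1% |
| 26 | 75.7% |
| 23 | 70.5% |

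The sizes 26 and 23 are illustrations. The article gives no expected deviation rate.

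**The case against.** The best defence is that little turns on any of this, and that a condensed article may leave the detail to a statistical analysis plan that is not shown. Much of that stands. Randomisation on day 0 should leave few participants undosed, and product is labelled by randomisation code, so errors in dispensing should be rare. Lists of deviations are normal content for an analysis plan. What the defence does not remove is that the article positively states an ITT safety analysis and a per-protocol set free of any deviation. These are rules fixed in the text, not gaps.

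Four stronger readings are tempting, and the documents do not support them:

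- **Events are collected only while on product.** The Safety assessment wording allows this, but the follow-up of withdrawn participants, the recording of events at visits and Table 1 leave it open.
- **ITT dilutes event rates most in the arm with more early stops.** Early stoppers have taken product, so changing the set does not affect them. They matter only if event collection ends with product, which is not established.
- **Two efficacy sets give two chances of success.** The article runs both ("Statistical analyses will be performed for both the ITT") and ties the primary t-test to neither, but it never says that a positive result on either would suffice. The ranking may well be in the analysis plan. Any inflated type I error calculated on that basis would describe a rule the article does not contain.
- **A late visit excludes a participant.** The article states no visit windows, so nothing shown makes a late visit a deviation.

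**Conclusion.** The point holds in a limited form. The safety set does not match exposure, the adverse event passages need reconciling, and the per-protocol definition is too strict as written. The safety effect is small: at most 1.8 percentage points in the illustration (20% shown as 18.2%), which rests on an assumed 3 of 33 undosed and an assumed 20% rate. The cost of the per-protocol rule cannot be sized from the article. It depends on how many deviations occur, and it matters less if that set is only supportive. None of this affects the sample size or shows that the trial's error rate is above 5%. It is worth correcting because the corrections are conventional and nearly free.

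**What to change.** 1. Safety set: replace ITT with all participants who took at least one dose, analysed by the product actually received.
2. Adverse events: reconcile the Safety assessment wording with the Subject withdrawal criteria and Safety outcomes sections, so that the text says plainly whether events after product is stopped are counted.
3. Per-protocol set: redefine it as participants without prespecified major deviations, listed in advance and classified before unblinding, and label it supportive to ITT.

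The cost is a few sentences and a blinded review of deviations before database lock. No added visits or participants are needed, and N = 66 stands.

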### Data and safety monitoring

To maintain the quality of this trial, monitoring will be conducted by Kyung Hee University Center for Clinical Research and Drug Development (KCRD; the CRO). Every institution participating in the trial will be monitored while this trial is in progress using standard operating procedures.

### Ethics

The present study has been approved by the institutional review boards (IRBs) at each of the three institutions, which are the Catholic University of Korea Seoul St Mary’s Hospital (reference KC12HNME0047), the Chung-ang University Hospital (reference C2011197), and the Kyung Hee University Hospital at Gangdong (reference KHNMC-OH-IRB 2011–019). Written informed consent will be obtained from each participant prior to enrolment. The trial will be performed in compliance with the Helsinki Declaration and according to Good Clinical Practice as described by the Korea Food & Drug Administration.

## Discussion

The present study seeks to investigate the clinical efficacy and safety of KM110329 for AD.

The desire for well-being and to improve one’s quality of life motivates consumers to purchase functional foods, thus opening an enormous new market.

The functional food market in Korea was introduced in the 1990s. It underwent the early stages of growth from 2002 to 2005, and it reached maturity in late 2006, valued at more than 1,280 billion Won. In the USA, the functional food market grows more than 6% annually, and it was estimated to reach 22.5 billion dollars in 2006 [16].

Despite the recent demand for functional food, there are only a few trial protocols to determine the clinical efficacy and safety of functional foods. In the present study, we will evaluate the efficacy of KM110329, a functional food consisting of four herbs that have been shown to be beneficial for skin health.

A study protocol for the treatment of AD using the herbal medicine Hwangryunhaedoktang has already been published [17], however, the present study has several distinctive features. First, this will be the first trial to investigate the efficacy of the functional food KM110329 for the treatment of AD. In the present study, we will assess not only the usual outcome measurements, such as SCORAD, DLQI, and IgE, but also TEWL and hydration in the stratum corneum to assess the overall health status of the skin.

Second, to the best of our knowledge, this will be the first trial protocol using KiFDA-HM-AD to evaluate severity of AD. KiFDA-HM-AD is an evaluation endpoint for clinical trials of herbal medicinal products related to AD [18]. The Korea Food and Drug Administration (KFDA) developed and deployed this assessment tool. This trial may provide a basic assessment of the reliability and validity of KiFDA-HM-AD by comparing the outcomes of the KiFDA-HM-AD with those of the SCORAD and DLQI.

We hope that this trial protocol will be a reference for designing further clinical trials for functional foods to improve skin health.

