Some studies have reported the components of KM110329 have effect on atopic dermatitis. Recent studies suggests that Rubi fructus regulates anaphylaxis and have anti-inflammatory effect [6,7]. Rehmanniae Radix prevents skin allergic reaction and treats allergen-induced atopic dermatitis in mice by suppressing the expression of cytokines, chemokines and adhesion molecules [8,9]. Houttuyniae Herba suppresses Th2 immune response and regulates inflammatory process [10,11]. Betulae Platyphyllae Cortex inhibits the development of atopic dermatitis-like skin lesions in NC/Nga mice through the suppression of the Th2 cell response. It also attenuates mast cell-mediated allergic inflammation in vivo and in vitro [12,13].

The aim of the present study is to determine the clinical efficacy and safety of KM110329 for AD.

We will conduct a randomised, double-blind, placebo-controlled, multicentre trial of KM110329 in adult patients with AD. Because of the absence of a gold standard for the treatment of AD, this trial will be conducted to determine the effectiveness of this functional food in comparison with a placebo-controlled group.

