### Sample size

Sample size calculations were performed to determine the number of participants needed to detect the effect sizes. We obtained an effect size from the previous study and based on the agreement of experts [14]. The results from the previous study were used to calculate the standard deviation [15]. The mean difference and standard deviation of the scoring atopic dermatitis (SCORAD) index were 10 and 13.576, respectively. The following formula was used to estimate the sample size.

$$\begin{array}{ll} n & =\frac{2{\left(z_{\alpha /2}+z_{\beta }\right)}^{2}\sigma^{2}}{{\left(\mu_{c}-\mu_{t}\right)}^{2}}\\ & =\frac{2\times {\left(1.96+0.84\right)}^{2}\times 13.576^{2}}{10^{2}}\\ & =28.932 \end{array}$$

The calculation was performed using 80% power, a 5% significance level, and a 10% dropout rate. The required sample size is approximately 33 participants for each group. Therefore, a total of 66 participants are needed for this trial.

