### Randomisation and allocation

The study subjects who satisfy the eligibility criteria will be randomised using a computer program at an independent centre (Kyung Hee University Center for Clinical Research and Drug Development; KCRD). Block randomisation with block size of 4 will be performed. The study subjects will be assigned to one of two groups with a 1:1 allocation ratio by investigator in each study site. Random numbers will be sent to each centre, and a randomisation table will be maintained by KCRD during the research period. Opaque sealed envelopes containing serial numbers will be delivered to each centre. The randomisation table kept in an opaque sealed envelope by the contract research organisation (CRO; KCRD) should be opened according to Standard Operating Procedures (SOPs).

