### Primary outcome measurement

The primary outcome in the present study is the change in the SCORAD index between the baseline (Visit 2) and after the treatment (Visit 5). The SCORAD index is a clinical tool for assessing the severity of atopic dermatitis as objectively as possible. The SCORAD index will be measured at every visit.

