### Secondary outcome measurement

Secondary outcome measurements include the change in the Dermatology Life Quality Index (DLQI), the total IgE level, eosinophil counts, IL-4, IL-5, IL-13, TEWL (Transepidermal Water Loss), hydration in the stratum corneum, and KiFDA-HM-AD. The study schedule is detailed in Table 1.

**Table 1 T1:** Study schedule of KM110329 clinical trial (8 weeks)

	**Screening**	**Treatment period**			
	**Visit 1**	**Visit 2**	**Visit 3**	**Visit 4**	**Visit 5**
	**(D − 7)**	**(D 0)**	**(D 7)**	**(D 28)**	**(D 56)**
**Informed consent**	**√**				
**Demographic characteristic eristic**	**√**				
**SCORAD index**	**√**	**√**	**√**	**√**	**√**
**Dermatology Life Quality Index**		**√**	**√**	**√**	**√**
**KiFDA-HM-AD**		**√**	**√**	**√**	**√**
**Laboratory tests**^ **1** ^	**√**	**√**			**√**
**Test for chronic hepatitis**^ **2** ^	**√**				
**Drug use history**	**√**				
**Concomitant medication**	**√**	**√**	**√**	**√**	**√**
**Pregnancy test**	**√**	**√**	**√**	**√**	**√**
**Medical/drug use history**	**√**	**√**	**√**	**√**	**√**
**Adverse event**			**√**	**√**	**√**
**Compliance calculation**			**√**	**√**	**√**
**Inclusion/exclusion criteria check**	**√**				
**Randomisation**		**√**			

^1^CBC (RBC, Hb, Hct, WBC, Platelet, ESR), Immunological tests (Eosinophil, IgE, IL-4, IL-5, IL-13), Liver function tests (AST, ALT), Renal function tests (BUN, Creatinine).

^2^Anti-HBs, HBsAg.

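### Comparing KiFDA-HM-AD with SCORAD and DLQI can show validity but not reliability, and the visit schedule gives no clean pre-treatment retest of the scale

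*Protocol article*

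**What the plan says.** The Discussion of the protocol article lists use of KiFDA-HM-AD as the second distinctive feature of the trial and adds: "This trial may provide a basic assessment of the reliability and validity of KiFDA-HM-AD by comparing the outcomes of the KiFDA-HM-AD with those of the" other two scales, SCORAD and DLQI. No other method for assessing the scale is given.

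The Background states the purpose of the trial: "The aim of the present study is to determine the clinical efficacy and safety of KM110329 for AD". KiFDA-HM-AD enters as the last item in the list of secondary outcomes ("hydration in the stratum corneum, and KiFDA-HM-AD").

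On timing, the section on the primary outcome says: "The SCORAD index will be measured at every visit". Table 1 agrees, with SCORAD ticked at Visits 1 to 5. In the same table KiFDA-HM-AD is ticked at Visits 2 to 5, and its Visit 1 cell is blank. Randomisation is at Visit 2.

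**The concern.** Reliability and validity are different properties and need different data. Validity asks whether a scale tracks what it is meant to track, and agreement with established scales speaks to that. Reliability asks whether the same scale gives consistent results, whether on repeat use in unchanged patients, between raters, or across its own items. The Discussion claims both properties and offers a method that serves only the first.

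The schedule does not make up for this. The only interval in which patients are seen twice before study product is Visit 1 to Visit 2, and KiFDA-HM-AD is missing from its first end. Every later repeat is taken on product or placebo, so within-patient differences mix measurement error with response.

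What is at stake is what can be concluded about the scale. If the text is followed as written, a between-scale correlation would stand as the evidence of reliability. The article presents itself as the first trial protocol to use the scale and hopes to serve as a reference for later trials, so the mistake could be carried forward.

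**Working it through.** **Inputs from the article**

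- Method for assessing KiFDA-HM-AD: comparison with SCORAD and DLQI (Discussion).
- Visit days: Visit 1 = D−7, Visit 2 = D0, Visit 3 = D7, Visit 4 = D28, Visit 5 = D56 (Table 1).
- Sample size: SCORAD difference and SD ("index were 10 and 13.576, respectively"), with "The calculation was performed using 80% power, a 5% significance level, and a 10% dropout rate" (Sample size).
- Allocation 1:1 (Randomisation and allocation).

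**Step 1: the plan's own figure.** The number of patients is needed only for the illustration in step 4.

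- With the printed z values, n = 2 × (1.96 + 0.84)² × 13.576² / 10² = 28.899. The printed 28.932 comes from unrounded z values, and the difference is immaterial.
- Rounded up this is 29 per group, and 29 / (1 − 0.10) = 32.2, so 33 per group and 66 in total. This agrees with "The required sample size is approximately 33 participants for each group". The figure reproduces, and the present point does not depend on it.

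**Step 2: method against property**

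| Comparison | What it informs |
|---|---|
| KiFDA-HM-AD with SCORAD or DLQI, same visit | Convergent validity |
| Change in KiFDA-HM-AD with change in SCORAD or DLQI | Responsiveness |
| KiFDA-HM-AD with itself, repeated in unchanged patients | Test-retest reliability |
| KiFDA-HM-AD between raters, or across its items | Inter-rater reliability, internal consistency |

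The Discussion names only the kind of comparison in the first two rows. The article describes no retest in stable patients, no second rater and no internal-consistency analysis.

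**Step 3: measurements before study product**

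| Scale | Visit 1 (D−7) | Visit 2 (D0) | Pre-treatment measurements | Pre-treatment pairs per patient |
|---|---|---|---|---|
| SCORAD | yes | yes | 2 | 1 |
| KiFDA-HM-AD | no | yes | 1 | 0 |

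The earliest pair available for KiFDA-HM-AD is Visit 2 to Visit 3 (D0 to D7), and its second value is taken after a week on product or placebo.

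**Step 4: illustration of precision.** The documents give no reliability figure, so the ICC is an assumption and is shown over a range. The Fisher-z approximation is used, with limits tanh(atanh(r) ± 1.96/√(n − 3)).

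- n = 66, r = 0.80: atanh(0.80) = 1.0986 and 1.96/√63 = 0.2469. The limits are tanh(0.8517) = 0.69 and tanh(1.3455) = 0.87.
- n = 33 (placebo patients only, D0 to D7), r = 0.80: 1.96/√30 = 0.3578. The limits are tanh(0.7408) = 0.63 and tanh(1.4564) = 0.90.

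| Assumed value | 66 pairs (Visits 1 and 2, if added) | 33 pairs (placebo, Visits 2 and 3) |
|---|---|---|
| 0.70 | 0.55 to 0.81 | 0.47 to 0.84 |
| 0.80 | 0.69 to 0.87 | 0.63 to 0.90 |
| 0.90 | 0.84 to 0.94 | 0.81 to 0.95 |

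Using n − 1.5 in place of n − 3, the form suited to an ICC from two measurements, leaves the 0.80 row unchanged to two decimals. These intervals describe sampling error only. They do not allow for placebo response in the right-hand column.

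**The case against.** The strongest reply is that this is an incidental remark. A reader might infer from the Discussion that assessing the scale is a trial aim that cannot be met. The documents do not support that reading, for two reasons.

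- **It is not an aim.** The Background gives efficacy and safety as the aim, and the Discussion opens by repeating it. The sentence on the scale is hedged twice (a possibility, and only a basic assessment), and KiFDA-HM-AD is one of several secondary outcomes. This stands in full.
- **Other routes to reliability may exist.** Internal consistency can be estimated from a single administration if the scale has several items. The article does not describe its structure, so this cannot be judged. A D0 to D7 retest could use patients in either arm whose SCORAD did not change, since both scales are taken at both visits. This also stands. But the text names neither route, and the D0 to D7 pair is weakened by treatment or placebo response even with a stability anchor.

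It can also be said that a journal article leaves psychometric detail to a fuller document. That would answer a complaint that detail is missing. It does not answer this point, because the article itself states a method and attaches to it a property that the method cannot show.

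Finally, the Visit 1 to Visit 2 pair would not be perfect. Table 1 checks eligibility at Visit 1 only, and entry requires objective SCORAD of at most 40. If the two scales correlate, some range restriction and regression to the mean would affect the estimate. This limits the proposed analysis but does not rescue the one in the text.

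**Conclusion.** The point holds in a limited form. The method in the Discussion supports a statement about convergent validity, or responsiveness if changes are compared, and does not support one about reliability. The schedule gives no KiFDA-HM-AD pair before study product, although SCORAD has one for every patient who attends Visits 1 and 2.

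The consequence is confined to what the trial can say about the scale. The primary outcome, the sample size of 66, the between-group comparison and the efficacy and safety conclusions are untouched. It would be wrong to conclude that reliability is beyond the trial's reach or that the design as a whole has failed.

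The conclusion on method rests on the text and Table 1 alone. The precision figures rest on an assumed ICC and on all 66 patients contributing a pair, so they are illustrative only.

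**What to change.** 1. In the Discussion, describe the comparison of KiFDA-HM-AD with SCORAD and DLQI as an assessment of validity only.
2. Then do one of the following:
   - add KiFDA-HM-AD at Visit 1 in Table 1 and state that reliability will be estimated as the Visit 1 to Visit 2 ICC, with a supporting analysis in patients whose SCORAD is stable between those visits; or
   - delete the reference to reliability. This is the remaining option if Visit 1 can no longer be changed.

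The first option costs one more use of an existing scale at an existing visit, perhaps a few minutes per patient (an estimate, as the article gives no completion time), and one simple analysis. Its report should acknowledge that patients were selected at Visit 1 on objective SCORAD of at most 40, so range restriction and regression to the mean may affect the ICC, and that the result applies to mild to moderate disease. The second option costs a change of wording. Neither affects treatment, the primary analysis or the sample size.
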